## Background

Low and intermediate grade chondrosarcomas (9-13% of all malignant bone tumours) are relative rare bone tumours. In 5-12% of all cases the chondrosarcomas are localized in head-and-neck region [1]. The typical sites of skull base lesions are temporo-occipital junction, parasellar area, spheno-ethmoid region and clivus [2,3]. Due to hystopathological type chondrosarcomas are divided into Grade 1 to 3 tumours according to mitotic rates (WHO classification) with 3 histological subgroups: classic, mesenchymal and myxoid [2]. The mesenchymal type has more aggressive growth behaviour and is associated with a poorer prognosis. Histological differentiation from chordomas is often difficult and must contain immunhistochemical staining [2,4]. Chordoma is immunopositive for epithelial markers like cytokeratin and endothelial membrane antigen (EMA), whereas chondrosarcoma is negative for both. Both chordomas and chondrosarcomas can be positive for S-100 and vimentin [5].

Most patients diagnosed are over the age of 40 years. Low grade chondrosarcoma has a low incidence of distant metastasis but is potentially lethal disease. Thus, local therapy has a crucial importance in the treatment of skull base chondrosarcomas. Surgical resection is the primary treatment standard. Unfortunately the late diagnosis and diagnosis at the extensive size of the tumours are common due to the slow growth kinetics; most patients are asymptomatic, or develop symptoms at a late stage of the disease. Consequently, complete resection is hindered due to close proximity to critical and hence dose limiting organs for radiation therapy i.e. optic nerves, chiasm and brainstem. Adjuvant or additional radiation therapy is very important for the improvement of local control rates in the primary treatment even after complete resection (no compartment resection possible). Anyhow, chondrosarcoma have a better outcome and prognosis compared to chordoma [6,7].

Chondrosarcomas are commonly radioresistant [8], and high local doses are required for long-term local control. Image guidance in conformal precision radiation therapy provides a safe technique in the treatment of base of skull tumours [9]. The highest dose conformality is possible using particle therapy with heavy ions and protons due to inverted dose profile allowing steep dose gradients and therefore providing further benefit in reducing toxicity and irradiation safety.

It is brightly accepted, that proton therapy can be considered the gold standard for treatment of rare skull-base tumours like chordoma and low grade chondrosarcoma [10]. Loma Linda University Medical Center (LLUMC) [8] the Massachusetts General Hospital (MGH) in Boston [11] have the longest experience in proton therapy for these entities. 3-year local control for chondrosarcomas after fractionated proton radiation therapy in 25 patients at LLUMC was 94% and the actuarial 5 year survival rate was 100% respectively [11].

The outcome in 229 chondrosarcomas treated with a combination of proton and photon therapy at MGH/HCL shows 5-and 10-year local progression free survival rate of 98% and 94% for chondrosarcomas respectively. The results are significantly better than in chordomas treated at the same institution [8].

Proton therapy results from PSI in Villingen, Switzerland were published by Weber et al. and Ares et. al. The data showed 3- and 5-year local control rates of 100% and 94%, respectively. 64 patients, among them 22 patients with chondrosarcoma were treated to a median target dose of 68.4 GyE. The 3-year actuarial overall survival rate for the chondrosarcoma patients was 91% [12,13].

Carbon ions though, have a higher biological effectiveness than either protons or photons, which is important in case of radioresistant tumours [14].

Carbon ion therapy is available at the National Institute of Radiological Sciences (NIRS) in Japan and at Heidelberger Ionenstrahl-Therapie (HIT) centre. The report of our Japanese colleagues experience is limited to 40 patients with chordoma and chondrosarcoma of the skull base. The patients could be treated effectively and without serious side effects [15]. NIRS beam delivery technique relies on passive scanning necessitating various modulators to adjust for treatment depth and tissue inhomogeneities within the beam path.

Our experience is based on the clinical work at the Gesellschaft für Schwerionenforschung (GSI) Darmstadt in Germany up to July 2008. In comparison to the Japanese centres, the facility at GSI as well as the HIT relies on active beam delivery using the raster-scan technique. About 300 patients with base of skull chordomas and chondrosarcomas have been treated so far. Initially, these patients were treated within a clinical Phase I/II study. After the study was able to demonstrate successful treatment, carbon ion therapy became approved as the best therapy available in Germany. The actuarial local control rates for the chondrosarcoma patients after 3 and 5 years was 96.2% and 89.8% respectively, the 5 year overall survival rates was 98.2% [16].

## Methods/Design

The study plan has been submitted to the ethics committee of the Medical faculty Heidelberg and is already approved. Also the positive vote of Bundesamt für Strahlenschutz (the governmental authority for radiation protection in Germany) has been already obtained.

The study is a double arm prospective randomised clinical phase III study of patients with low/intermediate grade chondrosarcomas of the skull base. Study patients are selected according to the inclusion criteria of the study protocol. After careful review of the patient reports and results of the additional examinations eligibility of a patient will be determined.

The randomisation will be done using the on-line randomisation tool (Randomizer.at) which is self-serve and runs exclusively on the Internet. The randomisation will be performed regarding treatment arms A and B. Patients will be randomized to the treatment groups with an equal allocation ratio of 1:1.

As this is an open-label study there will be no blinding of treatment assignment.

### Primary objectives of the study

The primary objective of this study is to evaluate, if the innovative therapy (carbon ion irradiation) in chondrosarcomas is not relevantly inferior to the standard proton treatment with respect to the 5 year LPFS rate defined as time from the randomisation to observed local recurrence. Withdrawals, lost to follow-ups and patients for whom no event has occurred at study termination are treated as censored observations. The censoring date is given by the last known date at which no event has occurred for the respective patient. Local recurrence defined as MRT or CT - morphological tumour progress in the former irradiated region. It is assumed that the LPFS rate for the proton therapy is 90%.

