### Study concept

Pre-treatment examination such as history and physical examination including neurological status, histological confirmation of chondrosarcoma, reference-histopathology if necessary, ophthalmologic examination by optic nerve, chiasm infiltration or by contiguity, audiometry by auditory channel infiltration or by contiguity, endocrinological examination by contiguity to sella turcica region and MR - Imaging (before) and after operation will be done or/and collected.

Patients with histologically confirmed low and intermediate grade chondrosarcoma and infiltration of the skull base which are willing to participate will be included into our study after verification of the eligibility centrally at the HIT trial center. These patients are subsequently randomized to one of the two treatment arms (arm A: carbon ion therapy, arm B: proton therapy).

Carbon ion therapy (Arm A) will be aplicated with a total target dose of 60 Gy E ± 5% to the PTV1. The PTV2 will receive a total carbon ion dose of 45 Gy E.

The patients entered in Arm B will receive proton therapy with the same target definition concept. The total proton dose will be 70 Gy E ± 5%. The PTV2 will receive a total dose of 50 to 56 Gy E in conventional fractionation.

Accrual period for the trial will be approximately 7 years. Our study design contains one interim analysis after observation period of approximately 5.5 years. The study will be terminated early in case of interim analysis showing 5% smaller rate of the 5 year LPFS of the experimental treatment (carbon ion therapy) in respect to the 5 year LPFS rate of standard treatment (proton therapy). If it is not a case the study ends with the enrollement of planned 154 patients. Definite assessments of 5 year LPFS, primary and secondary endpoints will be performed 12 years after completion of radiation therapy.

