## Organization and follow-up

Patient data will be collected and documented pseudonymously using electronic data processing (e.g. patient initials, date of birth and study number) at the study office at HIT.

The study data as for example all medical reports, RT documentation and CRF's will be collected at the study office at HIT.

Local recurrences will be confirmed radiologically and histologically whenever possible. At least two medical doctors (radiation oncologist and/or radiologist) will be required to judge of the recurrence or toxicity. Each adverse event occurring in connection with the therapy has to be documented, independent of the cause.

The first and the second follow-up examination will be performed 4-6 weeks and 3 months after completion of RT (follow-up 1 and 2). Follow-up examinations will then be scheduled after 6 months (follow-up 3), 9-12 months (follow-up 4), and then once a year for further 3 years (follow-up 5, 6 and 7). Additional visits will be scheduled as necessary. Acute toxicity is assessed at least weekly during RT and documented at the end of the RT series, 6 weeks after completion of RT and 3 months after RT. Late toxicity will be documented in regular intervals of 6 or 12 months during the observation period. All the patients will be observed for radiation specific acute and late AEs for the time of at least 5 years after irradiation. The maximum grade of toxicity will be determined for each patient.

The Common Terminology Criteria for Adverse Events V4.0 (CTCAE V4.0) will be used to grade acute toxicity from radiation therapy. The criteria are relevant from the 8th irradiation day until day 90, i.e. until the 1st follow-up visit. Thereafter, the RTOG/EORTC Criteria of Late Effects will be utilized. All acute radiation effects will be documented on an Acute Radiation Effect-Form. In addition, the AE-Form and/or SAE-Form will be filled out.

RTOG/EORTC Late Morbidity Scoring Scheme will be used to grade toxicity from radiation therapy occurring later than 90 days after its start, i.e. beyond the 1st follow-up visit. All late radiation effects will be documented on a Late Radiation Effect-Form. Every patient will be followed for LPFS and AEs for a time period of 5 years. Furthermore, patients will be followed for survival and locoregional recurrences for a time period of 5 years after completion of the irradiation.

Accrual period for the trial will be approximately 7 years starting in autumn 2010.

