## Discussion

Proton therapy is the standard treatment option in skull base chondrosarcoma patients after the tumour resection. Our experience with carbon ion therapy in patients with chondrosarcomas showed excellent results. However, until now, it has been not possible to compare both particles, i.e. protons and carbon ions, directly within the same facility for the treatment of low grade skull base chondrosarcomas.

This trial is a phase III study to demonstrate that carbon ion radiotherapy (experimental treatment) is not relevantly inferior and at least as good as proton radiotherapy (standard treatment) with respect to 5 year LPFS in the treatment of chondrosarcomas. Additionally, we expect less toxicity in the carbon ion treatment arm due to the reduced lateral scattering of the carbon beam.

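### The primary event is an unmasked judgement of progress in an irradiated region tied to no named volume, so counting of local recurrences could differ by arm, in a direction the protocol does not settle

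*Protocol article*

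**What the plan says.** Under Primary objectives of the study, the Protocol article gives the endpoint as the "5 year LPFS rate defined as time from the randomisation to observed local recurrence". The event itself is: "Local recurrence defined as MRT or CT - morphological tumour progress in the former irradiated region". The article does not say whether that region means CTV1, CTV2, a PTV or an isodose.

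Methods/Design states: "As this is an open-label study there will be no blinding of treatment assignment". Organization and follow-up sets the reading rule: "At least two medical doctors (radiation oncologist and/or radiologist) will be required to judge of the recurrence or toxicity". The sentence before it adds: "Local recurrences will be confirmed radiologically and histologically whenever possible". Two radiation oncologists would satisfy the rule. Masking to arm and independence from the patient's care are not required.

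Two other parts bear on the region. Study concept says: "The patients entered in Arm B will receive proton therapy with the same target definition concept". Treatment planning and radiation therapy gives one recipe for CTV1, CTV2 and PTV in all patients, with the CTV2 and PTV margins set individually.

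**The concern.** The primary event has two judgements in it: whether a change on imaging is progress, and whether it lies inside the region that counts. Both can be made by people who know the arm, and the second has no written boundary. A change near the edge of the treated area can be called local by one pair of readers and not by another. Organization and follow-up also censors patients with proven recurrence or metastases. Read with the event definition, a progression judged to lie outside the region would not be an event, and the patient would leave the risk set.

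In a non-inferiority trial with few expected events, unequal counting matters in both directions. Too few failures counted in the carbon arm makes a false claim of non-inferiority more likely. Too few counted in the proton arm makes a true claim harder to show.

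**Working it through.** **Inputs** (Statistical considerations, Methods/Design and Primary objectives): 154 patients allocated 1:1, so 77 per arm; proton 5-year LPFS 90%; assumed carbon advantage 7 points, so 97%; margin −5 points; one-sided 2.5% overall and 2.4% at the final analysis; sample size by Farrington-Manning.

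**1. The plan's own figure.** The restricted estimates under the null are 0.893 (carbon) and 0.943 (proton).
- s0 = √(0.893×0.107 + 0.943×0.057) = 0.386
- s1 = √(0.97×0.03 + 0.90×0.10) = 0.345
- n per arm = [(1.960×0.386 + 0.842×0.345)/0.12]² = 76.1, rounded up to 77, so 154 in total.

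The stated sample size is reproduced and is not in question.

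**2. Expected events with complete 5-year follow-up.**
- Design rates: 77×0.10 + 77×0.03 = 7.7 + 2.3 = 10.0
- Truth at the margin (proton 90%, carbon 85%): 77×0.10 + 77×0.15 = 7.7 + 11.6 = about 19

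**3. Effect of unequal counting.** Let a share k of true failures go uncounted in one arm only, so that the observed failure rate there is (1 − k) × the true rate. The rejection probability comes from exact binomial enumeration of the Farrington-Manning test, 77 per arm, at the 2.4% level, without the interim analysis. The shares k are assumptions; the document gives no misclassification rate.

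| Share missed | Carbon only, truth 85% v 90%: false non-inferiority | Carbon events missed | Proton only, truth 97% v 90%: power |
|---|---|---|---|
| 0% | 2.4% | 0 | 84.8% |
| 10% | 4.5% | 77×0.15×0.10 = 1.2 | 79.8% |
| 20% | 8.1% | 77×0.15×0.20 = 2.3 | 73.7% |
| 30% | 14.0% | 77×0.15×0.30 = 3.5 | 66.6% |

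The 84.8% is an exact figure. The normal approximation used for sample size gives 79.9% at the 2.4% level.

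**4. How many events would change the conclusion at the design rates.** The test statistic is z = [(e_P − e_C)/77 + 0.05]/SE, where e_P and e_C are the proton and carbon events and SE is the restricted standard error. With 8 proton events:
- 2 carbon: (0.0779 + 0.05)/0.0442 = 2.89, p = 0.002
- 4 carbon: (0.0519 + 0.05)/0.0461 = 2.21, p = 0.0135, still non-inferior
- 5 carbon: (0.0390 + 0.05)/0.0471 = 1.89, p = 0.029, above 2.4%

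From the expected split of 8 v 2, three additional carbon events are needed to lose non-inferiority.

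**The case against.** The strongest defence is that the irradiated region is naturally read as the treated target volume, which both arms draw by the same concept and recipe. The no-blinding sentence concerns treatment assignment and is ordinary for an open-label trial; it does not address image reading. Two readers are required and histology is sought where possible. Progression-free survival and patterns of recurrence are secondary, so progression outside the region would still be visible. A journal article may also leave reading procedures to the full protocol.

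Much of this stands as mitigation. It does not remove the point, because the article itself states the event definition and the reader rule. Neither fixes the boundary nor requires masking, and the secondary endpoints do not enter the primary test.

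Some stronger readings should not be drawn:
- A reader might infer that the carbon region is tighter, so that marginal failures count after protons but not after carbon. The Discussion expects less toxicity "due to the reduced lateral scattering of the carbon beam"; it says nothing about which recurrences count. The second-volume doses do differ by design (for carbon: "The PTV2 will receive a total carbon ion dose of 45 Gy E"), but the event is not defined by dose.
- A reader might infer that the treating doctors judge their own patients. The text does not say so; it only does not exclude it.
- A reader might infer that, with about 10 events, one or two reclassified cases decide the result. At the expected split this is wrong, as step 4 shows. One case decides only when the result already sits at the boundary.

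**Conclusion.** The point holds as a weakness in how the primary event is fixed. It is not an error in any stated figure. The region has no named volume and the judgement need not be masked, so ascertainment could differ by arm. The document does not establish that it will, or in which direction.

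If 10% to 20% of carbon failures alone went uncounted with the truth at the margin, the one-sided error would rise from 2.4% to between 4.5% and 8.1%. If the same shares of proton failures alone went uncounted under the design rates, exact power would fall from 84.8% to between 79.8% and 73.7%. The first range belongs to a scenario with about 19 events, not to the design expectation of about 10.

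These figures rest on assumed missed shares, complete 5-year follow-up and a binary test. The plan's own analysis uses Kaplan-Meier rates with a log(−log) interval, so they show the order of size and do not predict the trial's operating characteristics. The change is worth making because it is cheap and protects the primary comparison in both directions.

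**What to change.** 1. Have the two doctors already required read anonymised MR/CT images masked to arm. Where staffing allows, prefer readers who are not treating that patient. Take the event and its date from that reading.
2. Replace the irradiated region by a region common to both arms: CTV2, contoured by the shared concept, plus a fixed margin so that marginal recurrences count. Because the CTV2 margin is individual, contour it ideally before the arm is known. Keep the in-field/marginal classification for the secondary patterns of recurrence.

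**Cost:** a change of protocol wording, anonymising the images before the existing double reading, and small logistics. Keeping treating doctors out of the reading may call for other readers in some cases, which is why it is a preference. Masking may be imperfect. No extra patients or patient procedures are needed.

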### Secondary objectives of the study

Assessment of overall survival, progression free and metastasis free survival, patterns of recurrence, local control rate and morbidity (acute and late toxicity (Common Terminology Criteria for Adverse Events: CTCAE V4.0, RTOG/EORTC for late effects)) are the second objectives of the study. Plan quality (target coverage, sparing of organs at risk, integral dose) is also a matter of interest.

### Inclusion criteria

- Karnofsky Performance Score ≥60%

- Age >18 years and <80 years

- Informed consent signed by the patient

- Histological confirmation of low/intermediate grade chondrosarcoma with infiltration of the skull base.

### Exclusion criteria

- Inability to understand the aims of the study, no informed consent

- Prior RT of skull base region

- Other malignancies with disease-free interval < 5 years (excepting pre-cancerous lesions)

- Participation in another trial

- Pregnancy

- Simultaneous CHT or Immunotherapy.

### Study concept

Pre-treatment examination such as history and physical examination including neurological status, histological confirmation of chondrosarcoma, reference-histopathology if necessary, ophthalmologic examination by optic nerve, chiasm infiltration or by contiguity, audiometry by auditory channel infiltration or by contiguity, endocrinological examination by contiguity to sella turcica region and MR - Imaging (before) and after operation will be done or/and collected.

Patients with histologically confirmed low and intermediate grade chondrosarcoma and infiltration of the skull base which are willing to participate will be included into our study after verification of the eligibility centrally at the HIT trial center. These patients are subsequently randomized to one of the two treatment arms (arm A: carbon ion therapy, arm B: proton therapy).

Carbon ion therapy (Arm A) will be aplicated with a total target dose of 60 Gy E ± 5% to the PTV1. The PTV2 will receive a total carbon ion dose of 45 Gy E.

The patients entered in Arm B will receive proton therapy with the same target definition concept. The total proton dose will be 70 Gy E ± 5%. The PTV2 will receive a total dose of 50 to 56 Gy E in conventional fractionation.

Accrual period for the trial will be approximately 7 years. Our study design contains one interim analysis after observation period of approximately 5.5 years. The study will be terminated early in case of interim analysis showing 5% smaller rate of the 5 year LPFS of the experimental treatment (carbon ion therapy) in respect to the 5 year LPFS rate of standard treatment (proton therapy). If it is not a case the study ends with the enrollement of planned 154 patients. Definite assessments of 5 year LPFS, primary and secondary endpoints will be performed 12 years after completion of radiation therapy.

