## Statistical considerations

This trial is a phase III study to demonstrate that ion radiotherapy (experimental treatment) is not relevantly inferior to proton radiotherapy (standard treatment) with respect to the 5 year LPFS rate. The null-hypothesis to be assessed in confirmatory analysis states that the 5 year LPFS rate in the experimental treatment group is at least 5% lower than the 5 year LPFS rate in the standard treatment group. Confirmatory analysis for the primary end point is based on the intention-to-treat population. A group-sequential design is applied with one interim analysis after half of the expected number of events has occurred to allow for an early stopping of the study in case of an overwhelming treatment effect. The stopping rule is according to O'Brien and Fleming [18]. The one-sided critical level in the interim analysis is given by 0.26%, and in the final analysis it is given by 2.4%. Test decision is made by comparing the corresponding repeated confidence intervals to the boundary of the non-inferiority range of -5% (LPFS rate experimental treatment - LPFS rate standard treatment). With this design, the one-sided overall type I error rate is controlled by 2.5%. The confidence intervals for the differences between the LPFS rates are calculated based on the log(-log)-transformed Kaplan-Meier estimates of the rates using Greenwood's formula to estimate the underlying variance [19].

The total sample size of 154 patients provides a power of 80% to show non-inferiority of the experimental treatment to the standard treatment if the experimental treatment is in fact superior with respect to the 5 year LPFS rate by 7% and if the LPFS rate of the standard treatment group is 90%. Calculation of the sample size is based on the non-inferiority test for the differences between rates as described by Farrington and Manning [20].

If the confirmatory aim of the study cannot be reached, the trial still allows a descriptive head-to-head comparison of the two treatments, and the inspection of the confidence interval for the treatment effect enables to exclude a certain amount of difference in efficacy between the treatments.

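### The Protocol article gives two inconsistent rules for its one interim analysis, and the rule under Study concept acts on a bare point estimate that the power statement does not cover

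*Protocol article*

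**What the plan says.** **Study concept** (Protocol article) plans "one interim analysis after observation period of approximately 5.5 years" and gives one trigger for it: "The study will be terminated early in case of interim analysis showing 5% smaller rate of the 5 year LPFS of the experimental treatment", compared with proton therapy. It then disposes of every other result: "If it is not a case the study ends with the enrollement of planned 154 patients". No confidence level, interval or critical value is attached.

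**Statistical considerations** also has one interim analysis, timed at half the expected events, but its purpose is "to allow for an early stopping of the study in case of an overwhelming treatment effect". It adds "The stopping rule is according to O'Brien and Fleming", with one-sided levels of 0.26% at the look and 2.4% at the end. The decision is made by "comparing the corresponding repeated confidence intervals to the boundary of the non-inferiority range of -5" per cent, and the overall one-sided error is put at 2.5%. The section mentions no stop for an unfavourable carbon result. Its power statement (154 patients, 80%, carbon truly 7 points better than a 90% proton rate) mentions none either.

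**The concern.** Each section presents its rule as the whole interim rule, and each leaves out the other's exit. If carbon is observed 6 points worse, Study concept ends the trial and Statistical considerations continues it. If the efficacy boundary is crossed, Statistical considerations allows a stop and Study concept sends the trial on to 154 patients.

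The Study concept trigger is also weak as worded. It compares a raw difference in 5-year local progression-free survival (LPFS) rates with 5 points, at a time when few patients have been followed for five years, and it says the study will stop. At stake are three things: ending the trial by chance when the treatments are equal, losing the descriptive head-to-head comparison that Statistical considerations promises if the confirmatory aim fails, and a power figure that ignores one way the trial can end.

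**Working it through.** **1. The plan's own figures reproduce.**
- *Sample size.* Farrington-Manning, carbon 0.97, proton 0.90, margin 0.05. The restricted rates under the null are 0.8932 and 0.9432, so s0 = sqrt(0.8932×0.1068 + 0.9432×0.0568) = 0.386. Under the alternative, s1 = sqrt(0.97×0.03 + 0.90×0.10) = 0.345. Then n per arm = [(1.960×0.386 + 0.842×0.345)/0.12]² ≈ 76.1, which rounds up to 77, or 154 in total. Power at 77 per arm is 80.5% at 2.5% and 79.9% at 2.4%.
- *Error rate.* Critical values 2.794 (0.26%) and 1.977 (2.4%), with correlation sqrt(0.5), give an overall 2.50%.

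The efficacy design is therefore internally sound. The Study concept exit plays no part in these figures.

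**2. Information at the look.** The documents give 154 patients, 1:1 allocation, 7-year accrual and a look at about 5.5 years. Uniform accrual and calendar time from the first patient are assumptions.
- Enrolled: 154 × 5.5/7 = 121.
- With at least 5 years of follow-up: 154 × 0.5/7 = 11, or about 5-6 per arm.
- The event-based timing is roughly compatible. Half of 77×0.03 + 77×0.10 = 10.0 events is 5, and about 4.4 events are expected at 5.5 years under the design alternative. The conflict lies in direction and criterion more than in timing.

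**3. Rough closed form, both arms at 90%.** P(difference ≤ -0.05) = Φ(-0.05 / sqrt(2×0.9×0.1/n)). With n = 38 complete patients per arm (half of 77), this is Φ(-0.05/0.0688) = 23%. With n = 20 it is 30%.

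**4. Kaplan-Meier simulation.** 77 per arm, look at 5.5 years, no dropout, several thousand trials per case. Event times are exponential or Weibull. The Weibull shape comes from the carbon rates in Background (96.2% at 3 years, 89.8% at 5 years): ln(0.1076/0.0387)/ln(5/3) = 2.0.

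| True 5-year LPFS, carbon / proton | Chance the rule fires |
|---|---|
| 90% / 90% | about 26-31% |
| 94% / 94% | about 21-24% |
| 97% / 90% (design alternative) | about 3-6% |
| 85% / 90% | about 49% |

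At 90%/90%, roughly 46-64% of the stops rest on a net excess of at most two carbon recurrences.

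**5. Sensitivity (exponential times, both arms 90% unless stated).** The rule fires in 32% at the 5th event, 27% at the 8th event, 22% at 7 years and 18% at 8.5 years. It fires in 26% at 5.5 years with 2% annual dropout, and in 19% at 5.5 years if both arms are at 95%.

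**6. Effect on the confirmatory test.** Power loss is the probability that the interim difference is -5 points or lower and the final Farrington-Manning test at 2.4% would have succeeded. Under 97%/90% this is 1.6-3.3 points. Under 90%/90% the full trial has only about 17% power for non-inferiority. An additional stop without a claim of non-inferiority can only lower the chance of such a claim, so the type I error is not raised.

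**The case against.** A reader might infer that the two rules are opposites and cannot both hold. The documents do not support that. One design can carry an efficacy bound and an inferiority bound, and a result of -6 points cannot also cross the efficacy boundary, so applying both would never give conflicting orders. The defect is that neither section says both apply: the Study concept fallback leaves no efficacy exit, and Statistical considerations describes no inferiority exit.

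A second objection is that Study concept is a short summary in a condensed article. Its 5% equals the non-inferiority margin, so its wording may be a loose account of the repeated-interval comparison, which Statistical considerations specifies fully. This is a fair reason not to call the point-estimate rule deliberate. It does not explain why the direction of the stop is reversed, and both statements are current text.

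Third, a reader might infer serious damage to the confirmatory result, or an inflated type I error. Neither follows. The power loss under the design alternative is small, and under equality most stopped trials would have failed to show non-inferiority anyway. What is lost there is mainly precision for the promised descriptive comparison, with stopping that favours an estimate unfavourable to carbon.

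Finally, the false-stop percentages are not in the document. They depend on accrual pattern, event-time shape, true rate and the meaning of the 5.5-year observation period. That objection stands, and the percentages should be read as conditional.

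**Conclusion.** The inconsistency stands on the text alone and needs no simulation: one look has two differently directed rules, each written as if it were complete. It should be resolved before the interim analysis is run.

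The size of the problem, if Study concept were followed literally, is conditional on uniform 7-year accrual, a look at 5.5 calendar years, no dropout and the two event-time shapes. Over a quarter of trials with equal arms at the plan's own 90% would be ended. At a true 5-point deficit the rule would fire about as often as not, so it discriminates poorly at its own threshold. The loss from the stated 80% power is about 2-3 points. The case for change rests on the conflicting text and the missing uncertainty criterion; the power loss alone would not make it pressing. The documents do not settle which rule was intended.

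**What to change.** The sponsor should decide which interim exits are intended and state one identical rule in Study concept and Statistical considerations.

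If an inferiority or futility exit is intended alongside the efficacy bound:
- write it into Statistical considerations with an interval-based or predictive-probability criterion in place of the raw difference;
- say whether it is binding;
- check its operating characteristics by simulation, including how an arm with no events is handled, since Greenwood's variance is then zero and an interval rule can misfire;
- restate the power with the rule that is kept.

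The cost is a wording change, a short simulation and possibly a slightly lower stated power. There is a real trade-off: an interval-based criterion would stop a truly inferior carbon arm less often at the look. Under uniform accrual about 154 - 121 = 33 patients, some 16 of them on carbon, would still be to enrol then.
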